#### Radiotherapy

All patients are subjected to preparation of individual positioning devices and CT-based planning. Motion management may comprise either 4D-CT or midbreathing CT image acquisition. Further imaging modalities, such as FDG-PET/CT, may be used when deemed necessary. Gross tumor volumes (GTV) will be contoured and expanded by adequate clinical (CTV) and planning (PTV) safety margins in order to account for subclinical disease and positioning errors. No elective nodal irradiation will be performed. As for organs at risk, both lungs, spinal cord, heart and esophagus must be contoured. In the HYPO-arm, no more than 30% of “both lungs minus GTV” should receive > 20 Gy; in the CON-arm, no more than 35% of “both lungs minus GTV” should receive > 20 Gy.

In the HYPO-arm, 20 fractions of 2.75 Gy will be administered (total dose 55 Gy, corresponding to 70 GyBED, α/β = 10). In the CON-arm, 30 fractions of 2 Gy will be administered (total dose 60 Gy, corresponding to 72 GyBED, α/β = 10). Dose deviations of ±10% are acceptable, when clinically indicated. Radiotherapy is scheduled to start within 72 h after the first administration of durvalumab. Dose prescription will follow international reports (ICRU 50, 62 and 83). Both 3D-conformal and modulated photon radiation techniques, such as IMRT and VMAT/RapdArc, are acceptable. All participating institution are encouraged to perform regular, if no daily, positioning control using either portal imaging or on-board-CT devices.

### Study procedures

In order to minimize the risk exposure of patients when subjected to the hypofractionated radiation regimen, a safety lead-in phase with stop-and-go design will precede full enrollment into the HYPO-group (Fig. 2). Toxicity will be evaluated with a 6 + 6 design that is based on the statistical assumption that ≤1 event in *n* = 18 patients conforms to a non-toxicity scenario, with “event” being defined as the occurrence of pneumonitis grade ≥ 3 within 8 weeks after end of TRT. Consequently, two events in the first six patients or two events in the first 12 or two events in the first 18 patients will result in termination of the HYPO-group (Fig. 2).

During this safety stop-and-go phase, patients will be allocated to treatment arms as follows: While the HYPO-arm is recruiting, patients will exclusively enter this treatment group. During safety evaluation of the six patients of a HYPO-cohort (Stop/ Go decision), patients will be allocated to the CON-group only. If safety criteria in the HYPO-cohort are met, the HYPO-arm will be reopened to continue toxicity assessment, and patients will solely be allocated to this arm (Fig. 1). In order to avoid any bias, patients will be allocated centrally by the study management during this phase. If the non-toxicity criteria in the safety cohorts are met, the study will proceed to the expansion phase, and remaining patients will be randomized into the two treatment arms using an interactive web response system integrated in the electronic case report form (eCRF). A possibly uneven distribution of patients between the treatment groups at this stage will be compensated by a randomization strategy based on the “biased coin” method [15, 16]. In the randomization phase, patients will be stratified according to tumor stage (stage IIIA vs. stage IIIB/IIIC).

In total, 44 patients will be enrolled per group. After *n* = 18 patients have been enrolled to the HYPO- or CON-treatment arm, respectively, an interim efficacy analysis for the respective arm will be conducted based on the objective response rate (ORR) at 12 weeks after first durvalumab administration. In case of insufficient efficacy of one of the arms (i.e., the number of patients who have achieved a response is eight out of 18 or lower) this treatment arm will be terminated. Recruitment will be halted until results of the interim efficacy analysis are available.

Tumor response will be assessed according to RECIST 1.1 by CT and/ or MRI scans at baseline, 12 weeks after durvalumab initiation and then every 8 weeks. Safety measures will include physical examinations, performance status (ECOG), clinical laboratory profiles and continuous assessments of AEs. An overview of all study procedures is presented in Table 2.

An Independent Safety Monitoring Board (ISMB) will ensure the continued safety of participants throughout the trial. Data management and data quality assurance will be conducted following the Standard Operational Procedures of the Institute of Clinical Cancer Research IKF at Northwest Hospital GmbH (Frankfurt, Germany). An eCRF will be carefully maintained for each participant for data collection, also reporting serious and non-serious AEs following the common criteria for adverse events (CTCAE) version 5.0 throughout the entire trial. After the end of the study, participants will be proactively followed up regarding treatment-related AEs until resolved, returned to baseline or considered irreversible, until lost to follow-up, or withdrawal of study consent. All subjects will be followed for survival. Patients who decline to return to the site for evaluations will be offered a follow-up (FU) by phone every 3 months as an alternative. At the end of the study treatment, the investigators are responsible for the further treatment of the patient and must ensure that he or she receives appropriate standard of care or other appropriate therapies.

### Sampling for translational research

If patients participate in the translational research program, blood samples will be collected prior to cycles 1, 2 and 4 and at the time of disease progression (or end of treatment, EOT) along with stool samples (Table 2). Samples of untreated tumor lesions serving as baseline specimens will be collected as paraffin-embedded tissue. If re-biopsies are taken at the time of progression, samples should also be also submitted for translational research.

### Study endpoints

The primary endpoint of the study will be toxicity, defined by the occurrence of treatment-related pneumonitis grade ≥ 3. The ORR evaluated 12 weeks after first durvalumab administration (according to RECIST 1.1) is set as the primary efficacy endpoint. Secondary endpoints of the study comprise the occurrence of treatment-related AEs and serious AEs (SAEs), frequency of prespecified abnormal laboratory parameters, progression-free survival (PFS) and duration of clinical benefit, metastasis-free survival, overall survival (OS), and QoL.

Patient vulnerability and its association with survival and outcome will be assessed as an exploratory endpoint. To this end, the G8-screening questionnaire, a simple and fast screening tool for identifying geriatric risk profiles with a strong prognostic value for functional decline and OS in older populations with cancer, will be used [17]. Furthermore, biomaterials will be collected during the trial for correlation analyses on selected molecular parameters and clinical data in order to identify molecular biomarkers predictive for response to therapy. This approach is deemed appropriate to obtain hypothesis-generating data for future research due to the explorative character of this trial.

### Statistical analysis

#### Sample size justification

##### Safety run-in phase (HYPO-group)

With regard to the pneumonitis grade ≥ 3 rate, this phase is designed to distinguish between a toxicity scenario (pTox = 0.15) and a non-toxicity scenario (pTox = 0.035). A sample size of *n* = 18 will yield a probability of 0.78 to correctly detect the toxicity scenario, while the non-toxicity scenario will correctly be detected with a probability of 0.87. These probabilities are based on the decision rule that, if the number of patients with pneumonitis grade ≥ 3 in this cohort is ≥2, recruitment to the HYPO-group will be terminated.

##### Interim efficacy analysis regarding ORR and expansion phase

An interim efficacy analysis based on the ORR will be conducted after *n* = 18 patients in each arm have completed radiotherapy and the 18th patient has undergone first radiographic assessment (at 12 weeks after first durvalumab dose).

Previously, an ORR of 45% after radiotherapy alone has been reported in a Japanese population of elderly patients with unresectable stage III NSCLC [18]. Based on this and the observation that Asian ethnicity is associated with a favorable prognosis, we assume for the TRADE-hypo trial that an ORR higher than 0.42 in both treatment arms can be demonstrated, i.e. the null hypotheses for arm HYPO and CON are defined as H_0_
^HYPO^: π ^HYPO^ ≤ 0.42 and H_0_
^CON^: π ^CON^ ≤ 0.42, where π ^HYPO^ and π ^CON^ denote the actual ORR in arm HYPO and CON, respectively [19, 20]. Under the alternative hypothesis, it is assumed that both π ^HYPO^ and π ^CON^ amount to 0.60. Using an optimal Simon’s two-stage design with a one-sided significance level of α = 0.10 and a power of 1-β = 0.80 for each hypothesis test, *n* = 40 patients per arm are required, while the interim analysis is conducted after n = 18 patients per arm have been recruited to the trial. After successfully passing the safety analysis in the HYPO-group, if among 18 patients in the HYPO- or CON-arm, the number of patients who have achieved a response is eight or lower, the respective arm will be closed. Otherwise, an additional number of 22 patients will be enrolled into the respective arm. The null hypothesis of the respective arm can be rejected if at least 21 of all 40 patients per arm achieve a response. Sample size calculation was done using the R package “OneArmPhaseTwoStudy” [21].

To account for an estimated dropout rate of 10%, four patients will additionally be recruited to each treatment arm. Deviations from planned sample sizes will be handled as described by Englert & Kieser, allowing strict control of the aspired type I error rate in each arm [22].

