##### Methods of statistical analysis

The primary population for evaluating all efficacy endpoints and subject characteristics is defined as all patients enrolled according to initial allocation/randomization (intention-to-treat population, IIT). Secondary efficacy analyses will be carried out on the per-protocol (PP) population. The safety population comprising all patients who received at least one dose of the study medication will be used for all safety endpoints and will be analyzed according to the actual treatment received.

Response rates with confidence intervals (CI) and *p*-values in both study arms will be estimated taking into account the two-stage nature of the design [23, 24]. Secondary endpoints will be evaluated descriptively. All toxicities will be summarized by relative and absolute frequency, and severity grade based on CTCAE V5.0. AE and SAE summary tables will provide the number and percentage of patients with AEs and the 95% Clopper-Pearson type CIs. All analyses will be done using SAS version 9.4 (SAS Institute, Cary, NC) or higher.

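### Each arm is padded from 40 to 44 as if dropouts leave the analysis, but the primary ORR analysis keeps every enrolled patient, so the stated power of 0.80 need not hold

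*Protocol article*

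**What the plan says.** In the protocol article, the section on the interim efficacy analysis and expansion phase sets the null ORR ("we assume for the TRADE-hypo trial that an ORR higher than 0.42 in both treatment arms can be demonstrated") and an alternative of 0.60 in each arm. The design is described as follows: "Using an optimal Simon’s two-stage design with a one-sided significance level of α = 0.10 and a power of 1-β = 0.80 for each hypothesis test". This leads to 40 patients per arm, 18 in stage 1 and 22 in stage 2. The futility rule at stage 1 is that if "the number of patients who have achieved a response is eight or lower, the respective arm will be closed". The final rule is: "The null hypothesis of the respective arm can be rejected if at least 21 of all 40 patients per arm achieve a response".

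The same section then adds the allowance: "To account for an estimated dropout rate of 10%, four patients will additionally be recruited to each treatment arm". Study procedures gives the resulting total: "In total, 44 patients will be enrolled per group". Departures from the planned numbers are to be handled by a cited method, for which the article claims control of the type I error rate in each arm.

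Methods of statistical analysis defines the analysis set: "The primary population for evaluating all efficacy endpoints and subject characteristics is defined as all patients enrolled according to initial allocation/randomization". This is the ITT population.

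The interim is described in two ways. Study procedures and the Fig. 1 caption count 18 enrolled patients, and a later sentence of the sample size section counts 18 recruited. The opening sentence of that section instead requires 18 patients who have finished radiotherapy, the last of whom has had the first scan.

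**The concern.** Adding four patients so that about 40 remain is the logic of an evaluable-patient analysis: dropouts leave both numerator and denominator, and the remaining 40 respond at the assumed rate. Under ITT the dropouts stay in the denominator. If they have no week-12 response and count as non-responders, they lower the response rate that the test sees, and recruiting more patients at that lowered rate does not restore it. The only final boundary printed is for 40 patients, whereas the analysis set has 44.

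ORR at 12 weeks is the primary efficacy endpoint, and the rule at 18 can close an arm. At stake are whether the stated power belongs to the stated primary analysis, and how often an arm with the hoped-for activity would be closed or declared unsuccessful.

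**Working it through.** **Inputs from the protocol article.** Null ORR 0.42; alternative 0.60; one-sided alpha 0.10; power 0.80; stage 1 of 18, stop at 8 or fewer; reject at 21 or more of 40; dropout 10%; 44 enrolled per arm.

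**Assumptions the article does not state.** Patients without a week-12 response count as non-responders. Where marked below, 0.60 is the rate among evaluable patients.

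**Formula.** With X1 ~ Bin(18, p), X2 ~ Bin(n − 18, p) and final cut-off r:

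P(reject) = Σ over x = 9,…,18 of P(X1 = x) · P(X2 ≥ r − x).

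The chance of stopping for futility is P(X1 ≤ 8).

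**Step 1: the plan's own figure.** For n = 40 and r = 21, alpha at p = 0.42 is 0.0954 and power at p = 0.60 is 0.8001. An exhaustive search for the optimal Simon design returns the same 8/18 and 21/40. The stated design reproduces.

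**Step 2: what the padding implies.** 10% of 40 is 4, and 44 × 0.90 = 39.6, or about 40. The allowance restores 40 evaluable patients, which matters only if the test is run on them.

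**Step 3: boundary for 44.** At p = 0.42 with n = 44, r = 22 gives alpha 0.129 and r = 23 gives 0.087. The smallest cut-off that respects 0.10 is therefore 23. A conditional-error adjustment with a second stage of 26 leads to the same operating characteristics.

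**Step 4: power at 44 with r = 23.** With 10% dropout as non-responders, the ITT rate is 0.60 × 0.90 = 0.54.

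| Reading | Power |
|---|---|
| 0.60 is evaluable rate; interim on first 18 enrolled; rate 0.54 throughout | 0.560 |
| As above, but exactly four dropouts, two of them in the first 18 | 0.583 |
| 0.60 is evaluable rate; interim on 18 evaluable; then 22 evaluable plus exactly four dropouts | 0.659 |
| 0.60 is evaluable rate; interim on 18 evaluable at 0.60; then 26 enrolled at 0.54 | 0.716 |
| 0.60 is already the ITT rate | 0.806 |

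The last-but-one row is milder than the plan's allowance: it expects 26 × 0.10 = 2.6 dropouts, not four.

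Sensitivity of the first row to the dropout rate: 0.806 at 0%, 0.695 at 5%, 0.560 at 10%, 0.414 at 15%.

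**Step 5: does the padding help under ITT?** Without it, 21 of 40 enrolled at p = 0.54 gives power 0.557. With it, 23 of 44 gives 0.560. The four extra patients recover almost nothing.

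**Step 6: futility at 18.** P(X1 ≤ 8) is 0.135 at p = 0.60 and 0.281 at p = 0.54. The increase applies only if the 18 are the first 18 enrolled; with 18 evaluable patients it stays at 0.135.

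**The case against.** **The 0.60 may already be the ITT rate.** The article defines the parameter simply as the actual ORR in each arm, and the primary population is everyone enrolled. Read together, these give power of 0.81 at 44. This is a fair reading and it stands as a possibility, but the dropout allowance then has no purpose. One of the two statements has to give way.

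**Handling of missing scans is normally left to the full protocol or analysis plan.** Agreed; its absence from an article is not a fault in itself. The contradiction between sizing basis and analysis set is printed in the article all the same.

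**Only the alternative is diluted here, not the null.** If both rates describe evaluable patients, the null on the ITT scale is 0.42 × 0.90 = 0.378, and the 23-of-44 test has an exact alpha of only 0.028. It errs on the conservative side. Power can be partly recovered by rescaling the null as well: against 0.378, a cut-off of 21 of 44 has alpha 0.072 (20 gives 0.102, just over the limit), and power at 0.54 is 0.668. With the interim on the first 18 enrolled, that is still short of 0.80, and the article states the null as 0.42.

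**The cited method covers changed sample sizes.** It does so for type I error. A reader might infer that 21 responses will be applied to 44 patients and that alpha will be inflated. The article does not support this: directly after the dropout allowance it invokes a method to keep alpha under control when numbers deviate. Adjusting the boundary does not restore power.

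**Conclusion.** The contradiction between sizing basis and primary analysis set is real. Its effect on power depends on readings that the article leaves open. If 0.60 is the evaluable-patient rate, as the padding implies, and unassessed patients count as non-responders, power at 10% dropout is about 0.56 when the interim uses the first 18 enrolled, and about 0.66 to 0.72 when it uses 18 evaluable patients. On the first of these, the chance of closing an arm with the hoped-for activity roughly doubles, from 0.13 to 0.28. If 0.60 is the ITT rate, power is 0.81 and only the padding is redundant.

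A reader might conclude outright that the trial has 56% power. The article does not support that as an unconditional statement: it also needs dropouts to fall among the first 18, and the two descriptions of the interim disagree on this. Type I error is not shown to be at risk, and the toxicity endpoint is unaffected.

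**What to change.** Size and test on the same set. The protocol should:

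- state that the primary ITT test counts patients without a week-12 response as non-responders;
- state that 0.42 and 0.60 both refer to that ITT population, or, if 0.60 is the evaluable rate, restate power as about 0.56 to 0.72 according to the interim definition;
- say whether the interim 18 are the first 18 enrolled or 18 evaluable patients, and reconcile Study procedures and the Fig. 1 caption with the opening of the sample size section;
- replace the boundary for 40 by one recomputed for the actual ITT number, which is 23 if exactly 44 are analysed;
- drop the dropout justification for the four extra patients if 0.60 is declared to be the ITT rate.

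The cost is wording and possibly a less favourable stated power. No extra patients are needed.

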##### Methods of statistical analysis

The primary population for evaluating all efficacy endpoints and subject characteristics is defined as all patients enrolled according to initial allocation/randomization (intention-to-treat population, IIT). Secondary efficacy analyses will be carried out on the per-protocol (PP) population. The safety population comprising all patients who received at least one dose of the study medication will be used for all safety endpoints and will be analyzed according to the actual treatment received.

Response rates with confidence intervals (CI) and *p*-values in both study arms will be estimated taking into account the two-stage nature of the design [23, 24]. Secondary endpoints will be evaluated descriptively. All toxicities will be summarized by relative and absolute frequency, and severity grade based on CTCAE V5.0. AE and SAE summary tables will provide the number and percentage of patients with AEs and the 95% Clopper-Pearson type CIs. All analyses will be done using SAS version 9.4 (SAS Institute, Cary, NC) or higher.

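### If HYPO passes its pneumonitis gate, the pooled plain pneumonitis rate understates the true rate on average, and the plan neither adjusts for this nor shows patients before and after the gate separately

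*Protocol article*

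**What the plan says.** **The gate.** The section on the HYPO safety run-in states: "if the number of patients with pneumonitis grade ≥ 3 in this cohort is ≥2, recruitment to the HYPO-group will be terminated". Study procedures sets looks after each cohort of six and ends HYPO at any of them on a count of two: "two events in the first six patients or two events in the first 12 or two events in the first 18 patients will result in" (the words cut off say that the arm is closed). The event counted there is "the occurrence of pneumonitis grade ≥ 3 within 8 weeks after end of TRT".

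**The endpoint.** Study endpoints makes treatment-related pneumonitis of grade 3 or higher the primary endpoint of the trial and gives no time window.

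**The analysis.** Methods of statistical analysis summarises all toxicities by absolute and relative frequency and adds: "AE and SAE summary tables will provide the number and percentage of patients with AEs and the 95% Clopper-Pearson type CIs". The safety population is everyone who received at least one dose, so the lead-in patients are pooled with later ones. For response rates, by contrast, the same section says that estimates, intervals and p-values "will be estimated taking into account the two-stage nature of the design". No such provision is stated for pneumonitis.

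**The concern.** HYPO can reach its planned 44 patients only through a filter on pneumonitis. Whatever the true rate, the first 18 patients of an arm that passes bring at most one gate event into the final count. The other 26 are unfiltered. Pooling the two as if 44 had been a fixed sample pulls the point estimate down in the very situation in which HYPO is taken forward.

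At stake is the reading of the primary safety result. On the plan's own figures, a regimen with the unacceptable rate of 15% still passes with probability 1 − 0.78 = 0.22. The final estimate is then the remaining chance to notice the toxicity, and it is diluted by the favourable 18. CON has no pneumonitis gate, so its plain rate is not affected in this way.

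**Working it through.** **Inputs.** Gate: at most 1 event in 18 (safety run-in section). True rates: 0.15 and 0.035 (the plan's two scenarios), with 0.10 added as an intermediate value and 0.20 as a value beyond the range. Final size: 44 per arm (Study procedures), hence 44 − 18 = 26 patients after the gate.

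**The plan's own figures.** The pass probability is P = (1−p)^18 + 18p(1−p)^17. The looks at 6 and 12 do not change it, because a cumulative count cannot fall.
- p = 0.15: P = 0.0536 + 0.1704 = 0.224, so the toxicity scenario is detected with probability 0.776.
- p = 0.035: P = 0.5266 + 0.3438 = 0.870.

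The article says that 18 patients "will yield a probability of 0.78 to correctly detect the toxicity scenario, while the non-toxicity scenario will correctly be detected with a probability of 0.87". Both figures reproduce.

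**Mean pooled rate given a pass.** Let X1 be the number of events in the first 18. Given a pass, X1 is 0 or 1, and its mean is 18p(1−p)^17 / P, which simplifies to 18p/(1+17p). The later patients contribute 26p on average. The mean pooled rate is [18p/(1+17p) + 26p]/44.

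| True p | P(pass) | Mean X1 given pass | 26p | Mean pooled rate |
|---|---|---|---|---|
| 0.035 | 0.870 | 0.63/1.595 = 0.395 | 0.91 | 1.305/44 = 3.0% |
| 0.10 | 0.450 | 1.80/2.70 = 0.667 | 2.60 | 3.267/44 = 7.4% |
| 0.15 | 0.224 | 2.70/3.55 = 0.761 | 3.90 | 4.661/44 = 10.6% |

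The shortfalls are about 0.5, 2.6 and 4.4 percentage points. At p = 0.15 the pooled rate lies below the truth in 84% of passing trials, against 50% for a fixed sample of 44. With 40 instead of 44 evaluable patients, the mean at 0.15 is 10.2%.

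**Interval coverage given a pass (exact enumeration, n = 44).** Coverage of the 95% Clopper-Pearson interval is 99.4% at 0.035, 97.8% at 0.10 and 96.9% at 0.15. The lowest value on a grid of true rates from 0.01 to 0.15 is 93.2%. At 0.20 it is 89.4%.

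**All stopping paths together.** At p = 0.15, arms that stop at the end of a cohort show a mean plain rate of 23.1%. The overall mean is 0.776 × 23.1% + 0.224 × 10.6% = 20.3%. At p = 0.035 the overall mean is 4.7%. Unconditionally, the bias is upward.

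**What a UMVUE would do.** For 4 events in 44 after a pass, the UMVUE is C(26,3) / [C(26,4) + 18·C(26,3)] = 2600/(14950 + 46800) = 4.2%. The plain rate is 4/44 = 9.1%.

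**Patients after the gate.** Given a pass, their outcomes are unfiltered, so their plain rate is unbiased. Clopper-Pearson coverage at n = 26 is 97.5% at 0.15 and 98.8% at 0.035.

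**The case against.** **The interval.** A reader might infer that the Clopper-Pearson interval is invalid. The figures do not support this. Over the range the run-in was built for, coverage given a pass is about 93% or better, and over all paths it is at least 96.4% on the same grid. The one poor value, 89.4%, needs a true rate of 20%. That lies above both design scenarios, and such a regimen passes only about 10% of the time.

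**The direction.** A reader might infer that the plan generally understates pneumonitis. Over all outcomes it does the reverse. Any go/no-go rule leaves a conditional bias after a go. This stands, and it is why the point is limited to an arm that passes.

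**The endpoint.** The gate and the primary endpoint are not identical: one has an 8-week window, the other is restricted to treatment-related events and states no window. Events in the first 18 patients after 8 weeks would escape the filter and make the bias smaller. This also stands.

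**The comparison.** A reader might infer that the plan's comparison of the arms is distorted. The article plans no between-arm test; the response hypotheses are set arm by arm and toxicity is described. The bias in HYPO's own estimate remains all the same.

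**The source.** The quoted sentence concerns adverse event tables in general, and an analysis plan that is not shown may split lead-in from later patients. The article does nothing to exclude that. It does, however, state how all toxicities are summarised and in which population, and it reserves design-adjusted estimation for response.

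**Conclusion.** The point holds as a conditional bias of the point estimate. If HYPO passes its gate and reaches 44, the pooled plain rate of grade 3 or higher pneumonitis is too low on average: 10.6% for a true 15%, 7.4% for 10%, 3.0% for 3.5%. In the non-toxicity scenario, where 87% of arms pass, the shortfall is about half a point and of little consequence. It matters if the gate has let a toxic regimen through.

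The figures assume independent patients, a common true rate before and after the gate, 8-week event status equal to final status, all 44 patients evaluable, no stop for insufficient response, and no pneumonitis stopping after patient 18 (none is stated). The stopping rule and the sample size are not affected. This is a modest matter of interpretation that is cheap to put right.

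**What to change.** 1. Besides the pooled rate, report HYPO pneumonitis of grade 3 or higher separately for the first 18 patients and for patients from number 19 on (about 26), each with a Clopper-Pearson interval. Define the split by enrolment number, because the Fig. 2 legend lets full enrolment open after 12 event-free patients.
2. State beside the pooled rate that it is conditional on the arm having passed the gate.
3. If HYPO is set beside CON, use the post-gate HYPO patients together with CON patients randomised over the same period. CON patients allocated during the lead-in were not randomised.
4. Do not carry over a UMVUE by analogy with the design-adjusted response analysis. It removes bias over all paths, and in a passing arm it lowers the estimate further (9.1% to 4.2% in the example above).

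The cost is one extra table split and less precision. As an illustration, take 4 events in 44, one of them before the gate. The pooled result is 9.1% (95% interval 2.5% to 21.7%). Split, it is 1/18 = 5.6% (0.1% to 27.3%) and 3/26 = 11.5% (2.4% to 30.2%).
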